## Introduction

### Background and rationale {6a}

The carpal tunnel is an anatomical space located at the base of the palm of the hand, delimited by a rigid floor and walls, the carpal bones, and a roof with a certain capacity for distension, the transverse carpal ligament or flexor retinaculum. The entrance of the tunnel is located between the scaphoid and pyramidal bones, and its exit between the trapezium and hamate bones. A number of anatomical structures pass through this relatively narrow space as it transitions from the forearm to the hand: the tendons of the superficial and deep flexor muscles of the fingers, the tendon of the long flexor muscle of the first finger, and the median nerve [1]. Thus, an increase in volume within this space, however small, can lead to compression of the nerve [2].

The dimensions of the carpal tunnel are 20 mm at the level of the hook of the hamate, narrow compared to the proximal (24 mm) or distal (25 mm) dimensions [3]. In healthy individuals the intratunnel pressure ranges between 3–5 mmHg in neutral position [4]; vascular compromise of the nerve begins when the pressure exceeds 20–30 mmHg [5], which could be favored by certain postures or gestures as common as using a computer mouse [6]. Adjacent musculature may also play a role in the etiology; in a cadaver study, the muscle belly of the flexor digitorum superficialis was observed to access the proximal tunnel during wrist extension, similar to the lumbrical muscles observed in contact with the distal tunnel during metacarpophalangeal flexion [7].

The median nerve is responsible for the sensory innervation of the first three fingers and the radial border of the fourth, which is why patients who suffer compression of the median nerve inside the tunnel report pain and hypoesthesia in these fingers. The palm of the hand, however, usually remains unaltered, as it is innervated by a sensory cutaneous branch that emerges 6 cm proximal to the entrance of the nerve into the tunnel [5].

Carpal Tunnel Syndrome (CTS) is the most common compressive neuropathy, accounting for 90% of all neuropathies [1,8]. It is estimated that 1 in 5 patients with symptoms of pain, paresthesia and numbness of the hand will be diagnosed with CTS based on examination and an electrodiagnostic test [8].

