### Sample size {14}

To calculate the sample size (EPIDAT program) we proposed:

Expected sensibility: 78%Expected specificity: 87%Level of confidence: 95%

In order to evaluate ultrasound as a diagnostic test versus neurophysiological study in patients with a high clinical suspicion of suffering from CTS, expected values of sensitivity and specificity of the ultrasound test of 78% and 87% respectively, a maximum precision of 5% and a confidence level of 95% are considered, resulting in the need to evaluate a minimum of 264 patients with a positive result in the nerve conduction study as well as a minimum of 174 patients with a negative result, which means a total sample of 438 patients (Table 3). The number of positive and negative tests were known because the results were analysed by a secondary investigator. Therefore, the secondary investigator would indicate whether it was necessary to continue appointing patients for ultrasound scans until the total number of patients in both groups were obtained.

**Table 3 pone.0281221.t003:** Sample size.

Precision (%)	Sample Size		
	Positive test	Negative test	Total
5.000	264	174	**438**

The calculation was performed using the EPIDAT software, considering the parameters that underlie the calculation of the required sample size for conducting a diagnostic test evaluation study. The parameters requested by the software are based on sensitivity, specificity, and precision, which were obtained from previous studies.

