### Recruitment {15}

The patients included in the study will be obtained consecutively through the consultations of the Neurophysiology Department of the Virgen Macarena Hospital (Seville, Spain), provided that they have clinical suspicion of CTS.

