#### Plans to promote participant retention and complete follow-up {18b}

Not applicable. The data collection is a one-time ultrasound and the are no further revisions or assessments scheduled after. Initially, patients undergo neurophysiological testing. Therefore, the Neurophysiology Service refers the patients 1 to 3 months after the neurophysiological test has been performed. Subsequently, patients are contacted by the principal investigator to schedule the ultrasound scan. If the patient attends the ultrasound, he/she is included in the sample. Otherwise, the patient is not included.

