## Statistical methods

### Statistical methods for primary and secondary outcomes {20a}

After an initial exploration of the data, quantitative variables are expressed as means and standard deviations or medians and quartiles in case of asymmetric distributions, and qualitative variables as percentages.

The calculation of the measures of test accuracy of the ultrasound test as a diagnostic test for CTS: sensitivity, specificity, predictive values and likelihood ratios, are carried out considering the neurophysiological study as the reference test (gold standard).

Likewise, the reliability of the ultrasound is analyzed by calculating the degree of agreement between the diagnoses of the two tests using Cohen’s Kappa coefficient. The concordance of both tests with the established clinical severity is also studied.

The analysis of the quantitative variables did not present normality (Gaussian assumptions), therefore, for statistical inference, the Mann Whitney test (violations of Gaussianity) was used for independent quantitative variables. Shortly afterwards, a multivariate logistic regression model will be created to try to determine the best subset of them that predict CTS [20].

Finally, ROC curves will be performed to evaluate cut-off points for certain quantitative ultrasound parameters that discriminate well against CTS. In the ROC curves, the optimal cut-off point for greater sensitivity and specificity was determined by using the Youden index. In those ultrasound parameters where the ROC curve did not allow adequate discrimination, the median value of the data distribution was used.

In summary, the univariate analysis aims to identify which ultrasound parameters are related to the result of the CTS, thus providing elements of analysis to determine the cut-off points to be evaluated by means of ROC or medians, as well as the main variables to be considered in the multivariate model.

Data analysis is performed with SPSS 25.0 statistical software.

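### If enrolment closes separately at 264 NPT-positive and 174 NPT-negative patients, predictive values from the study table reflect the precision formula and not the clinic; the article leaves open whether it does

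*Protocol article*

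**What the plan says.** Sample size {14} plans for a sensitivity of 78% and a specificity of 87%, and adds that "a maximum precision of 5% and a confidence level of 95% are considered". It arrives at a minimum of 264 NPT-positive and a minimum of 174 NPT-negative patients and gives the total as 438. Table 3 and the Abstract repeat that total.

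The same section says that a secondary investigator, who has the NPT results, indicates whether to "continue appointing patients for ultrasound scans until the total number of patients in both groups were obtained". The section on unblinding {17b} confirms that this person decides when the sample is complete.

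Recruitment {15} describes the sampling differently: patients "will be obtained consecutively through the consultations of the Neurophysiology Department". The Abstract and the consent section {26a} also call recruitment consecutive. No section says that a patient whose NPT group is already full is turned away.

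Statistical methods {20a} then lists the accuracy measures, with NPT as the reference: "sensitivity, specificity, predictive values and likelihood ratios". Cohen's kappa is added as the measure of agreement. The section does not tie the predictive values to any prevalence.

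**The concern.** Sensitivity, specificity and likelihood ratios condition on the reference result, so the mix of NPT-positive and NPT-negative patients does not change what they estimate. Predictive values condition on the ultrasound result, and they depend directly on that mix. If the mix is set by two enrolment targets, the predictive values from the study table belong to a population that the design created.

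These are the figures a reader would use to decide whether an ultrasound result could spare a patient the NPT. The article's rationale points that way: the background cites long waits and costs for NPT, and the discussion considers ultrasound as a first-line or screening test.

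**Working it through.** **Inputs.** From Sample size {14}: "Expected sensibility: 78" per cent, "Expected specificity: 87" per cent, precision 5%, confidence 95%. The article does not give the department's NPT-positive share, so every share below other than 60.3% is an assumption.

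**1. The plan's own figure.** With n = z²·p(1−p)/d², z = 1.96 and d = 0.05:
- NPT positive: 3.8415 × 0.78 × 0.22 / 0.0025 = 263.68, rounded up to 264.
- NPT negative: 3.8415 × 0.87 × 0.13 / 0.0025 = 173.79, rounded up to 174.
- Total: 264 + 174 = 438. This reproduces exactly.

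No prevalence enters. The positive share is 264/438 = 60.3%, which equals 0.1716/(0.1716 + 0.1131), the ratio of the binomial variances. It carries no information about the clinic.

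**2. Expected table at 264/174.**
- Ultrasound positive: 0.78 × 264 = 205.92 true and 0.13 × 174 = 22.62 false. PPV = 205.92/228.54 = 90.1%.
- Ultrasound negative: 0.87 × 174 = 151.38 true and 0.22 × 264 = 58.08 false. NPV = 151.38/209.46 = 72.3%.

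**3. Same test, other NPT-positive shares π.** Write se and sp for sensitivity and specificity.
- PPV = se·π / [se·π + (1−sp)(1−π)]
- NPV = sp(1−π) / [sp(1−π) + (1−se)π]
- Kappa = (po − pe)/(1 − pe), where po = se·π + sp(1−π), t = se·π + (1−sp)(1−π) and pe = tπ + (1−t)(1−π)

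| NPT-positive share | PPV | NPV | Kappa |
|---|---|---|---|
| 20% (assumed) | 60.0% | 94.1% | 0.58 |
| 40% (assumed) | 80.0% | 85.6% | 0.65 |
| 50% (assumed) | 85.7% | 79.8% | 0.65 |
| 60.3% (264/174) | 90.1% | 72.3% | 0.63 |
| 70% (assumed) | 93.3% | 62.9% | 0.59 |
| 80% (assumed) | 96.0% | 49.7% | 0.51 |

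**4. The other reading: keep every consecutive patient until both minimums are met.** About max[264/π, 174/(1−π)] patients are needed: 264/0.20 = 1320, 264/0.40 = 660, 174/0.20 = 870 at π = 80%, and 438 only at π = 60.3%. A simulation of this rule (2000 runs per share) gave these mean totals:

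| Clinic share | Mean total |
|---|---|
| 20% | 1319 |
| 40% | 661 |
| 50% | 528 |
| 60% | 455 |
| 70% | 580 |
| 80% | 868 |

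The sample share stayed within about 0.15 percentage points of the clinic's, so predictive values from the table were essentially unbiased. The total of 438 was approached only near 60%.

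**The case against.** The strongest reply is that no quota is written down. The targets are minimums, recruitment is consecutive, and the secondary investigator's role can be read as one continue-or-stop decision for the whole study. The 438 would then be the sum of two minimums and not a cap. Step 4 shows that the objection to the predictive values largely disappears on that reading. This stands: capping by group cannot be treated as established. What it does not explain is a total stated three times that this reading would exceed unless the clinic's share is near 60%.

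It is also fair that the primary objective concerns accuracy, that the sample size rests on sensitivity and specificity alone, and that predictive values are one item in a list. A separate analysis plan might also say how they are derived. As written, {20a} reads most naturally as computing them from the study table.

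Four stronger readings are tempting, and the article does not support them:
- *The predictive values will be wrong for this clinic.* That needs both closure by group and a share away from 60%. Neither is documented.
- *The clinic's share is 20%.* The background says: "It is estimated that 1 in 5 patients with symptoms of pain, paresthesia and numbness of the hand will be diagnosed with CTS". That is a general statement about symptomatic people. The study patients have been referred for NPT, and {14} describes their clinical suspicion as high.
- *Kappa is seriously distorted.* It stays between 0.58 and 0.65 for shares of 20% to 70%. It falls to 0.51 only at 80%.
- *Non-attendance adds a bias that needs weighting.* Section {18b} says: "If the patient attends the ultrasound, he/she is included in the sample. Otherwise, the patient is not included". This could shift the share if attendance differed by NPT result, but nothing in the article shows that it does.

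**Conclusion.** The point holds in a conditional form. Consecutive recruitment, minimums of 264 and 174, and a total of 438 are compatible only if the clinic's NPT-positive share is near 60%, so the article must say which of them governs. If enrolment closes by group, PPV and NPV from the study table are fixed near 90.1% and 72.3% whatever the clinic's share, given the planning sensitivity and specificity.

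The size of the resulting bias is unknown. It is near zero at about 60%. Under an assumed 20% share, the table would overstate PPV by 30.1 points (90.1 − 60.0) and understate NPV by 21.8 (94.1 − 72.3). Under an assumed 80% share, it would understate PPV by 5.9 points (96.0 − 90.1) and overstate NPV by 22.6 (72.3 − 49.7). Sensitivity, specificity and likelihood ratios are unaffected by the split on either reading.

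**What to change.** - In Sample size {14} and Recruitment {15}, state whether enrolment stops separately for each NPT group. If it does, describe the sampling as stratified by NPT result. If it does not, state that 438 is a lower bound and that all consecutive patients are kept.
- In Statistical methods {20a}, do not take PPV and NPV from the raw table. Compute them by Bayes' rule from the estimated sensitivity and specificity, at the NPT-positive share among consecutive eligible patients where that count is available. Otherwise give them over a stated range of prevalences.
- Report kappa together with the NPT-positive and NPT-negative counts behind it.

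The cost is mainly wording, with no new patients or scans. The article does not mention a register of all eligible patients, so the count may not be obtainable; the prevalence range covers that case. The downside is that the predictive values become conditional on a stated prevalence and may look less favourable.

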### Recruitment {15}

The patients included in the study will be obtained consecutively through the consultations of the Neurophysiology Department of the Virgen Macarena Hospital (Seville, Spain), provided that they have clinical suspicion of CTS.

## Methods: Assignment of interventions (for controlled trials)

### Sequence generation {16a}

Not applicable, since there are no intervention groups. All patients we recruited from the neurophysiology department of the Vigen Macarena Hospital (Seville, Spain), who underwent an ultrasonography following a specific protocol.

### Concealment mechanism {16b}

Not applicable, since there are no intervention groups.

### Implementation {16c}

Not applicable, since there are no intervention groups.

## Assignment of interventions: Blinding

### Who will be blinded {17a}

Not applicable. This protocol is for an evaluation study of diagnostic tests comparing electroneurography and ultrasound. Nevertheless, the result of the neurophysiological study will be blinded so the principal researcher does not know the expected outcome of the ultrasound (results of the neurophysiological testing).

### Procedure for unblinding if needed {17b}

Not applicable. No unblinded procedure will be carried out due to the diagnostic nature of the study but the results of neurophysiological testing are analysed by a secondary researcher who determines when the sample is fully collected.

## Methods: Data collection, management, and analysis

### Data collection methods

#### Plans for assessment and collection of outcomes {18a}

The means necessary to carry out our study will be a Sonosite ultrasound scanner model X-porte, ultrasound gel and a computer for data collection in Excel table.

In order to promote data quality, a training period was included for the researcher in charge of performing the ultrasounds, it was carried out during the first period of the timeline.

On the other hand, when the ultrasound was performed, 3 measurements were made of each parameter, taking the average of the three of them.

Of the instruments included in the study, the following should be highlighted:

Boston Carpal Tunnel Questionnaire–(BCTQ):

The Boston scale is a validated and self-administered questionnaire that assesses the impact of CTS on both symptoms and patient function [13], having demonstrated a statistically significant relationship between AST, NF, clinical symptoms and hand functionality [14,15]. There are 11 questions, each with 5 possible answers, each answer gives a score and the final sum gives a probability of having CTS. Contrary to the above, Mondelli et al. in 2008 [16] obtained results when comparing the combination of ultrasound and NF versus BCTQ, finding no relationship between the questionnaire and the other two tools.

However, more publications support the usefulness of BCTQ, being a tool translated into several languages such as Arabic, Turkish or Japanese [17].

Of the tests used in the physical examination the following should be highlight:

Tinel sign: this test is performed by lightly tapping on the median nerve to provoke a tingling sensation or "pins and needles" in the nerve distribution. The sensitivity is between 26 and 79% and the specificity is between 40 and 100% [18].Phalen sign: is a provocative test used in the diagnosis of CTS. The patient places her elbows flexed on a table, allowing her wrists to fall into maximum flexion and is asked to push the dorsal surface of her hands together and hold this position for 30–60 seconds. This position will increase the pressure in the carpal tunnel, effectively compressing the median nerve between the transverse carpal ligament and the anterior border of the distal end of the radius. The test is positive when a tingling or prickling sensation is felt in the distribution of the nerve. The sensitivity is between 67 and 83% and the specificity is between 47 and 100% [18,19].

#### Plans to promote participant retention and complete follow-up {18b}

Not applicable. The data collection is a one-time ultrasound and the are no further revisions or assessments scheduled after. Initially, patients undergo neurophysiological testing. Therefore, the Neurophysiology Service refers the patients 1 to 3 months after the neurophysiological test has been performed. Subsequently, patients are contacted by the principal investigator to schedule the ultrasound scan. If the patient attends the ultrasound, he/she is included in the sample. Otherwise, the patient is not included.

### Data management {19}

The data will be entered by one of the two principal investigators, in batches of 50 patients, performing a subsequent review of the data to ensure that there are no errors when entering them.

We will not use the patient’s personal data but the personal health code (NUSHA).

The storage will be done in Excel format on a computer and on an external storage system (USB).

## Statistical methods

### Statistical methods for primary and secondary outcomes {20a}

After an initial exploration of the data, quantitative variables are expressed as means and standard deviations or medians and quartiles in case of asymmetric distributions, and qualitative variables as percentages.

The calculation of the measures of test accuracy of the ultrasound test as a diagnostic test for CTS: sensitivity, specificity, predictive values and likelihood ratios, are carried out considering the neurophysiological study as the reference test (gold standard).

Likewise, the reliability of the ultrasound is analyzed by calculating the degree of agreement between the diagnoses of the two tests using Cohen’s Kappa coefficient. The concordance of both tests with the established clinical severity is also studied.

The analysis of the quantitative variables did not present normality (Gaussian assumptions), therefore, for statistical inference, the Mann Whitney test (violations of Gaussianity) was used for independent quantitative variables. Shortly afterwards, a multivariate logistic regression model will be created to try to determine the best subset of them that predict CTS [20].

Finally, ROC curves will be performed to evaluate cut-off points for certain quantitative ultrasound parameters that discriminate well against CTS. In the ROC curves, the optimal cut-off point for greater sensitivity and specificity was determined by using the Youden index. In those ultrasound parameters where the ROC curve did not allow adequate discrimination, the median value of the data distribution was used.

In summary, the univariate analysis aims to identify which ultrasound parameters are related to the result of the CTS, thus providing elements of analysis to determine the cut-off points to be evaluated by means of ROC or medians, as well as the main variables to be considered in the multivariate model.

Data analysis is performed with SPSS 25.0 statistical software.

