## Objectives {7}

**Primary**: To assess the accurancy of ultrasound in the diagnosis of CTS with respect to nerve conduction studies.

Secondary:

To determine the set of ultrasound parameters (ultrasound standards and reference values) that best predict the existence of CTS.To evaluate the relationship between the intensity or degree of involvement between ultrasound findings and nerve conduction studies.To propose a standardised protocol for the study of CTS by ultrasound.To perform a descriptive cost-effectiveness analysis between ultrasound and neurophysiological studies in the diagnosis of CTS.To detect and describe qualitative anatomical alterations and pathological findings that could predispose to the presence of CTS.

**Hypothesis**: Ultrasound is more accurate than neurophysiological studies in the diagnosis of CTS.

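### Youden cut-offs are chosen and scored on the same patients against the same neurophysiological result, with no optimism correction named

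*Protocol article*

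**What the plan says.** Section {20a} of the protocol article computes sensitivity, specificity, predictive values and likelihood ratios of ultrasound; these "are carried out considering the neurophysiological study as the reference test (gold standard"). Kappa between the two diagnoses follows. Parameters are then screened one by one, a logistic model looks for the best subset, and ROC curves supply cut-offs for the parameters that discriminate well: "In the ROC curves, the optimal cut-off point for greater sensitivity and specificity was determined by using the Youden index". Where a ROC curve does not discriminate adequately, the sample median is used instead.

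The Objectives {7} make accuracy of ultrasound primary, and add as a secondary aim: "To determine the set of ultrasound parameters (ultrasound standards and reference values) that best predict the existence of CTS". Sections {6b} and the Discussion define CTS by a positive NPT, so the ROC outcome and the reference test are the same label.

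Sample size {14} plans one sample, with "a maximum precision of 5% and a confidence level of 95% are considered", giving "a minimum of 264 patients with a positive result in the nerve conduction study as well as a minimum of 174 patients" (the latter group NPT-negative). No split, cross-validation, bootstrap or external validation is described. The one cut-off that the authors adopt in advance is 1.4 for the wrist-forearm index (Discussion). For CSA the Discussion gives only a published range of 9 to 15 mm², and for retinaculum bulging the cut-off is left to be found in the study.

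**The concern.** A quantitative parameter calls a patient positive or negative only through a cut-off. The Youden rule picks the cut-off at which sensitivity plus specificity is largest in these patients, and part of that maximum is chance. If the same patients then supply the accuracy estimate, it averages above what the same cut-off achieves in new patients. Choosing the best of several parameters on the same data adds a second layer.

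Two things are at stake. The sample size rests on an interval calculation that treats the cut-off as given, and tuning it on the data erodes that coverage. The reference values are also meant for use elsewhere, so other centres would adopt cut-offs with a published performance that they should not expect to see.

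**Working it through.** **Inputs.** From Sample size {14}: "Expected sensibility: 78" and "Expected specificity: 87" (per cent), half-width 5 points, 95% confidence, 264 NPT-positive and 174 NPT-negative patients. The protocol gives no distributions for the ultrasound parameters, so the shapes, AUCs and correlations below are assumptions.

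**Step 1: the plan's own figure.** n = z² p(1 − p) / d², with z = 1.96 and d = 0.05.
- Sensitivity: 3.8416 × 0.78 × 0.22 / 0.0025 = 263.7, rounded up to 264.
- Specificity: 3.8416 × 0.87 × 0.13 / 0.0025 = 173.8, rounded up to 174.
- Total 438, as stated. The formula is for a proportion at a cut-off fixed in advance.

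**Step 2: a parameter with its true optimum at 78%/87%.** Negatives are N(0, 1). At the Youden optimum the two densities are equal. The cut-off is c = Φ⁻¹(0.87) = 1.126, and its standardised position among positives is Φ⁻¹(0.22) = −0.772. The positive SD is φ(−0.772)/φ(1.126) = 1.400, and the positive mean is 1.126 + 0.772 × 1.400 = 2.207. The AUC is Φ(2.207/√(1 + 1.400²)) = 0.90.

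**Step 3: simulation.** Draw 264 positives and 174 negatives, take the empirical Youden cut-off, and compare apparent accuracy with true accuracy at that same cut-off. Coverage is the share of runs in which the usual 95% interval contains that true value.

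| Case | Excess sensitivity (points) | Excess specificity (points) | Coverage of 95% interval |
|---|---|---|---|
| One parameter, 78%/87% | about 1.1 | about 1.6 | about 91% / 87% |
| One parameter, true Youden index 0.80 | 1.0 | 1.2 | 89% / 87% |
| One parameter, true Youden index 0.30 (AUC about 0.70) | 1.6 | 2.3 | 90% / 90% |
| Best of four, AUC 0.90 down to 0.75-0.80, correlation 0.45 | about 1.2-1.4 | about 1.8-2.0 | about 88-91% / 89-90% |
| Best of four or five, all AUC about 0.90 | about 2-3 | about 3-3.5 | about 79-81% / 73-76% |
| Best of five, all AUC about 0.70 | about 3.2 | about 4.5 | about 80% / 76% |

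In one run of the first case, apparent accuracy averaged 79.0%/88.0%, against 77.8%/86.6% true at the chosen cut-off. Repeat runs move the excess by 0.1 or so and the coverage by about one percentage point. With a cut-off fixed in advance, this excess is zero by construction.

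**The case against.** Much can fairly be said in the plan's favour.

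- *The rule does not reach every parameter.* Doppler uptake, notches and masses need no cut-off, the wrist-forearm index is fixed at 1.4, and poorly discriminating parameters go to the median, which is not chosen to maximise agreement with NPT. This stands. A reader might infer that weak parameters gain most and that their ranking is thereby distorted. The median rule prevents that conclusion for the parameters it catches. Because no threshold for adequate discrimination is given, a parameter with an AUC near 0.70 could still be Youden-tuned, but that is not certain.
- *The bias is small beside the planned precision.* For one good parameter it is 1 to 2 points per measure against 5. This stands. A reader might add the two excesses and call the sum comparable to the 5-point margin, but that margin applies to sensitivity and specificity separately.
- *Best of five equals is close to a worst case.* Outcomes measures {12} lists five quantitative parameters; with the index fixed at 1.4, at most four are tuned. The Discussion does not treat them as equal either: it cites work placing CSA above the others, with dissent, and calls bulging findings inconclusive. The equal-AUC rows are therefore an upper range. Section {20a} also does not say that a single best parameter will stand for ultrasound.
- *The link to the primary result is inferred.* The section never says outright that Youden cut-offs define a positive ultrasound. This stands as a limit, but apart from 1.4 and the median they are the only route given for a quantitative parameter.
- *Internal validation could sit in an unseen analysis plan.* That would excuse silence. Here the article states the cut-off rule, and followed as written it produces the optimism.

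**Conclusion.** The point holds in limited form. Youden cut-offs are tuned and scored on the same patients against the same NPT result, so sensitivity and specificity at those cut-offs are optimistic. The excess is about 1.1 and 1.6 points for one parameter at the planned accuracy, with 95% intervals covering about 91% and 87%. It grows modestly if the best of several unequal parameters is reported, and to about 2-3 and 3-3.5 points if several are equally good at an AUC of about 0.90. It is larger at lower AUC.

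These sizes rest on assumed normal distributions, AUCs and correlations; the direction does not. A reader might conclude that the trial's reported accuracy will be too high overall. The documents do not support that, because net bias also depends on errors in NPT as the reference, which this point does not address. Severity: should be fixed, since it bears on the primary objective and on the reference values, but the size is modest.

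**What to change.** Amend {20a} in one of two ways.

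1. Report the primary sensitivity and specificity at cut-offs written down before NPT results are linked to the ultrasound data, as is already done with 1.4 for the wrist-forearm index, and label Youden cut-offs exploratory. For CSA this means committing to one value within a wide published range and giving the reason.
2. Keep the Youden cut-offs, but report optimism-corrected accuracy from cross-validation or a bootstrap in which every resample repeats the parameter selection and the choice of Youden or median cut-off. Show uncorrected figures only beside the corrected ones. Smoothing the ROC curve is optional.

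Parts of {20a} are in the past tense, which suggests that some data may already have been examined. If NPT results have been linked, the second route is the one that remains. A simple bootstrap may correct only partly: in the 78%/87% case it recovered 1.9 of 2.7 points of the combined excess.

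Cost: a few sentences and some scripting, with no new patients or measurements. The headline accuracy will probably be one to a few points less favourable.
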